### Future Directions

Although the content is different, the platform’s addiction courses have user home page interfaces that have the exact same layout as that of the arm 1 home page interface. If the results from our study indicate that members engage with the prompts and nudges in arm 2 and arm 3, we will replicate this experiment with new members who register for these courses. Although the addiction courses focus on problem drinking and smoking cessation, the use of nudges and prompts to increase engagement may be generalizable to many digital health courses that focus on addictions and mental health.

The secondary and tertiary outcomes will help shape the development of future nudges and prompts. If specific types of nudges and prompts are appealing to specific gender and demographic groups, we will customize the content for these groups and analyze their effectiveness in future studies.

We are currently employing natural language processing to analyze identifiable contexts (ie, change talk) in our communities [52]. We will apply the findings from that experiment to the member-generated content from the goals and diary tools to better determine the types of prompts and nudges that result in engagement among members. The overall goal will be to use artificial intelligence to train the platform to recognize different usability patterns and show specific engagement prompts and nudges to stratified populations.

The goal of the courses is to promote wellness and increase access to efficacious, self-guided support for people with depression and anxiety. The focus of the study is restricted to testing whether nudges and prompts increase engagement. If the study is successful, future research will need to determine if nudges and prompts contribute to decreases in depression and the frequency and intensity of panic attacks.

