### Power and Sample Size

Our goal is to obtain 0.95 power to detect a significant difference in the proportion of users who complete at least 1 cognitive behavioral therapy session between the two treatment groups (arm 2 vs arm 3). Based on a preliminary analysis of an early subsample of users from November 1 to December 9, 2021 (arm 1: n=510; power=3.14%; arm 2: n=484; power=5.79%) and a conventional α level (.05) for statistical significance, we would require a sample of 4224 users, with 1414 users in each treatment group. Multimedia Appendix 1 shows our study’s CONSORT-EHEALTH (Consolidated Standards of Reporting Trials of Electronic and Mobile Health Applications and Online Telehealth) checklist [50].

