### Primary Outcome: Engagement With Tips and To-do Items

We will first measure engagement with the tips and to-do items in arms 2 and 3. We will compare the frequency of engagement with each nudge and behavioral prompt by age and gender. A member’s engagement with tips will be measured as the proportion of tips that were clicked. Specifically, it will be a value between 0 and 1, calculated as the number of tips that a member clicked divided by the number of tips that were presented to the member. Engagement with to-do items will be measured as the number of to-do items that a member clicked, and course component completion rates will be measured as the number of course components that a member completed. All comparisons between arms 2 and 3 will be conducted by using an independent sample 1-tailed *t* test; a conventional α level (.05) for statistical significance will be used.

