### Tertiary Outcomes: Engagement With Types of Tips

Another outcome of this experiment is to determine what types of tips are most engaging (directive, social proof, or present bias tips). We will assess this by comparing engagement with the tips in arm 2 and arm 3 via a 1-way ANOVA in which the types of tips are used as the independent variable. We will then assess if age and gender predict which type of tip is the most engaging by using multiple regression.

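### The age and gender regression for the most engaging tip type cannot separate a group's preference for a type from its general tendency to click; a type-by-group interaction is needed

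*Protocol article*

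**What the plan says.** Three parts of the protocol article bear on this.

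- **Exposure (Intervention Groups).** Arm 2 shows 35 directive tips. Arm 3 shows 15 social proof and 15 present bias tips, and also has a to-do checklist. No member sees all three tip types.
- **Analysis (Secondary Outcomes and Tertiary Outcomes).** After a one-way ANOVA by tip type, both sections end with the same sentence: "We will then assess if age and gender predict which type of tip is the most engaging by using multiple regression". The primary outcome section also has a by-group look: "We will compare the frequency of engagement with each nudge and behavioral prompt by age and gender". It names no test or significance level for that look. The t test and the .05 level in that section belong to the arm 2 versus arm 3 comparisons.
- **Use of the result (Future Directions).** "If specific types of nudges and prompts are appealing to specific gender and demographic groups, we will customize the content for these groups". The same sentence goes on to say that the effectiveness of the customised content will be studied later.

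**The concern.** The trigger for tailoring is that a *type* appeals to a *group*. That is a statement about differences between differences: the gap between types must vary with age or gender. The regression as described has age and gender as predictors, and the plan names no interaction with tip type.

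If women, say, click more on every tip, a regression for a given type will show a gender coefficient although there is no preference. If some of those coefficients pass .05 and others do not, the pattern looks like a group preference. The next round of content would then be built on a group split that does not exist.

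**Working it through.** **1. Can the stated regression answer its question?** The article does not define the dependent variable. The natural readings are these.

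- *Outcome is the member's most engaging type.* For every arm 2 member the only possible value is directive; for every arm 3 member it is one of the other two. Arm is randomised, so age and gender can be related to directive versus not directive only by chance. The regression is uninformative about directive tips.
- *One regression of click proportion per type.* Each age or gender coefficient measures how much the group clicks on that type. A general clicking tendency enters all three.
- *One pooled regression with type, age and gender as main effects.* The age and gender coefficients are averages over types and say nothing about preference.

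Only social proof versus present bias can be compared within a member, and only in arm 3. Regressing that within-member difference on age and gender would be a valid preference analysis, but it is an interaction analysis and the article does not describe it.

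**2. How often would per-type tests mislead?** The plan gives no figure for this analysis, so there is none to reproduce. The one input from the plan is 1414 members per group (Power and Sample Size). As a check on that input, 3.14% versus 5.79% at 0.95 power and α = .05 gives 1387 per group one-sided with continuity correction, 27/1414 = 1.9% below the stated number.

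Assumptions, not in the documents:
- genders balanced, so 1414/2 = 707 each per arm;
- the same gender shift d (in SD units) for all three types, so no true preference;
- correlation 0.5 between a member's social proof and present bias proportions;
- per-type two-sided tests at .05.

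Expected test statistic: d / √(2/707) = 18.80 × d. Power p per type follows from the normal distribution. If the three tests were independent, the chance that some but not all are significant would be 1 − p³ − (1 − p)³. Simulation adds the 0.5 correlation.

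| Shift d (SD) | 18.80 × d | p per type | Split, independent formula | Split, simulated |
|---|---|---|---|---|
| 0.05 | 0.94 | 0.16 | 0.39 | 35–36% |
| 0.10 | 1.88 | 0.47 | 0.75 | 64–66% |
| 0.125 | 2.35 | 0.65 | 0.68 | 61–62% |
| 0.15 | 2.82 | 0.80 | 0.47 | 43% |
| 0.20 | 3.76 | 0.96 | 0.10 | 9–10% |
| 0.30 | 5.64 | >0.99 | 0.00 | near 0% |

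A joint type-by-gender test in the same setting is positive in about 5% at every shift.

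**3. Reading the table.** The split rate peaks where each test has power near one half and vanishes when the shift is large. At 0.20 to 0.30 SD nearly all three tests are significant; that is no evidence of a preference either, but it is less likely to be read as one. More members per arm would move the peak to a smaller shift without removing it.

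**The case against.** **Retesting is planned.** The sentence on customising goes on to promise evaluation in later studies, and the default home page decision (Practical Implications) depends on whether prompts are used, not on age or gender. This stands. The harm is a misdirected next study, not unchecked adoption.

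**A reader might infer that subgroup tests run with no hierarchy and that false differences will probably be acted on.** The article does not support this. Outcomes are ranked primary, secondary and tertiary, and the tip-type question is tertiary. No test or level is attached to the age and gender comparisons. With an assumed .05 per test, 6 tests (3 types × 2 characteristics) give a chance of at least one false positive of 1 − 0.95⁶ = 0.27 if independent and 0.14 at correlation 0.8. For 8 tests (4 types × 2) the figures are 1 − 0.95⁸ = 0.34 and 0.16. That is material but not probable. Only counting every single tip and to-do item makes it likely on most assumptions, whereas the tailoring rule speaks of types. A missing correction or exploratory label is also detail that an analysis plan not shown may hold.

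**Separate per-type tests are not stated in the plan.** True; they are the most workable reading of an undefined regression. The simulated range illustrates that reading and is not a property of a procedure that the article fixes.

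**Model detail belongs in the analysis plan.** This answers the multiplicity point but not the mismatch. The article names a method and a question, and by its own account of what each arm sees, age and gender main effects do not answer that question.

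**Conclusion.** The point holds as a mismatch between method and question. Age and gender main effects cannot show that a tip type appeals to a particular group, because each member sees only the types of one arm and because general clicking enters every coefficient. This rests on the article's own text and needs no assumption about effect size.

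The size of the consequence does depend on assumptions. With a common gender shift of 0.05 to 0.30 SD and no true preference, per-type tests are split in about 0% to 65% of trials, against about 5% for an interaction test. Because the tailored content is to be studied again, the cost is a spurious group split carried into the next study. The documents do not support a claim that false differences will probably be acted on, or that the plan has no ranking of outcomes.

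**What to change.** In Secondary Outcomes and Tertiary Outcomes, replace the shared regression sentence with the following.

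- One model of tip-click proportion, with one record per member per tip type and a member random effect or clustered standard errors. Terms: tip type, age, gender, type × age and type × gender.
- Claims that a type appeals to a group rest only on the two interactions, Holm-adjusted at .05 (the smaller p-value against .025, then the larger against .05). All these analyses are labelled exploratory.
- A statement that social proof versus present bias is a within-member comparison in arm 3, whereas any contrast with directive tips is also arm 2 versus arm 3 and includes the effect of the to-do checklist. The model does not remove that confounding; it can only be declared.

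In Future Directions, tie customisation to an adjusted interaction. The evaluation in later studies is already there and should stay.

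The cost is wording and one model, using age, gender and click data already collected. The downside is fewer nominally significant subgroup results.

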## Appendix

Multimedia Appendix 1 CONSORT-eHEALTH checklist (V 1.6.1).

## Abbreviations

CONSORT-EHEALTH: Consolidated Standards of Reporting Trials of Electronic and Mobile Health Applications and Online Telehealth
